## Abstract

**Background:**

Public transport (PT) users typically accumulate more physical activity (PA) than private motor vehicle users yet redressing physical inactivity through transport-related PA (TRPA) interventions has received limited attention. Further, incentive-based strategies can increase leisure-time PA but their impact on TRPA, is unclear. This study's objective is to determine the impact of an incentive-based strategy on TRPA in a regional Australian setting.

**Methods:**

*trips4health* is a single-blinded randomised controlled trial with a four-month intervention phase and subsequent six-month maintenance phase. Participants will be randomised to: an incentives-based intervention (bus trip credit for reaching bus trip targets, weekly text messages to support greater bus use, written PA guidelines); or an active control (written PA guidelines only). Three hundred and fifty adults (≥18 years) from southern Tasmania will be recruited through convenience methods, provide informed consent and baseline information, then be randomised. The primary outcome is change in accelerometer measured average daily step count at baseline and four- and ten-months later. Secondary outcomes are changes in: measured and self-reported travel behaviour (e.g. PT use), PA, sedentary behaviour; self-reported and measured (blood pressure, waist circumference, height, weight) health; travel behaviour perspectives (e.g. enablers/barriers); quality of life; and transport-related costs. Linear mixed model regression will determine group differences. Participant and PT provider level process evaluations will be conducted and intervention costs to the provider determined.

**Discussion:**

*trips4health* will determine the effectiveness of an incentive-based strategy to increase TRPA by targeting PT use. The findings will enable evidence-informed decisions about the worthwhileness of such strategies.

**Trial registration:**

ACTRN12619001136190.

**Universal trial number:**

U1111-1233-8050.

## Background

1

Physical inactivity is one of the most significant global health concerns, causing 6–10% of coronary heart disease, type 2 diabetes and breast and colon cancers [1]. Physical inactivity poses a similar risk for premature mortality as smoking and obesity and in 2013 was estimated to cost the international community in productivity losses and health care system costs INT$67.5 billion [1,2]. Despite abundant initiatives to support population level increases in physical activity (PA) (e.g. “Life. Be in it”, “This Girl Can”, “International Walk to School Day”), little progress has been made. For instance, the proportion of Australians (aged 15 years and older) adhering to PA guidelines is basically unchanged since the 1980s at around 35–40% [3]. Initiatives to redress physical inactivity have principally focused on leisure-time and sporting activities, with much less attention given to other domains of PA such as transport [4].

Many international, national and state-based frameworks for PA promotion highlight the important impact that active travel (e.g. cycling, walking) supportive environments can have on daily PA [[5], [6], [7], [8]]. Active commuters have significantly lower cardiovascular risk than passive commuters [9] and up to 33 min/day of PA is accumulated through use of public transport according to a recent systematic review [10]. Transport-related PA represents an attractive but under-explored opportunity to support individuals to make small changes that collectively can positively impact population health. While transport-related PA is discretionary, travelling from place to place is commonly a necessary daily behaviour. Drawing on dual process theory, individuals may be more likely to persist with regular PA if it is associated with a habitual pattern, such as travel [[11], [12], [13]].

Incentive-based strategies have demonstrated some promise for improving health behaviours in adults, but relatively few high-quality studies have focused on PA and none specifically on incentivising public transport use for PA gain [[14], [15], [16], [17], [18], [19], [20], [21]]. In a 2017 survey on travel behaviour and health involving 1091 Australian adults, 42.4% of participants rated an incentive-based strategy as likely/extremely likely to increase their public transport use, ranking it as one of the top three public transport use enhancement strategies in the survey [22]. How best to implement incentive-based strategies to increase public transport use for PA gain in real-world settings is unestablished. Behavioural economics theory purports that humans suffer from ‘present bias’, and therefore immediate rather than delayed gratification may be more likely to change behaviour (23,24). Behaviour change may also be more likely when incentives are frequent and progressively escalated [20,23,24]. Incentive-based strategies are also more likely to succeed when supported by other proven behaviour change techniques (e.g. goal-setting, self-monitoring, social support [25]).

*trips4health* is a single-blinded randomised controlled trial designed to fill a knowledge gap and respond to a stakeholder identified need regarding the impact of an incentive-based strategy on public transport use for PA gain. The study findings will benefit service providers, policymakers and practitioners.

## Objectives

2

The aim of *trips4health* is to establish the impact of an incentive-based strategy (rewarding greater public transport use) on transport-related PA.

## Trial design

3

Single-blinded controlled trial.

## Materials and methods

4

Participants, interventions and outcomes.

## Study setting

5

The study will be implemented within the greater area of Hobart, the state capital of Tasmania (Fig. 1). Tasmania is a regional island state of Australia with approximately 510,000 people of which just under half live in the study area [26]. Tasmania has some of the highest rates of chronic disease in Australia and is characterised by high levels of socioeconomic disadvantage [27]. The only mode of public transport is bus, with metropolitan services predominantly offered by one provider (Fig. 1). In 2016, 5.3% of employed residents within the greater Hobart area were estimated to commute by bus as a single method of transport, compared with 76% estimated to commute by driving a car [28].

**Fig. 1 fig1:**
[figure not shown]
Study Setting: The Greater Hobart area with public transport accessibility identified. Hobart city;  Urban public transport zone;  Non-urban public transport zones;  Greater Hobart Region.

## Eligibility criteria

6

Prospective participants’ eligibility will be determined via an online or telephone screening questionnaire (Fig. 2). Inclusion criteria include: ≥ 18 years old; sufficient English proficiency to provide informed consent; living in Southern Tasmania; able to access an urban Tasmania bus service (participant defined); making trips by motor vehicle that could be made by bus; current infrequent bus user (on average ≤ 2 trips per week in the past six months); possession or willingness to possess a public transport smartcard; willingness for the public transport provider and the researchers to access smartcard data; possession of a mobile phone. Exclusion criteria include: intending to move house or work location whereby an urban bus service in Southern Tasmania will be inaccessible within the 10-month study period; currently engaged in or planning to engage in other incentive-based programs to enhance public transport use; pregnancy; a health condition that prevents walking; a health condition that prevents bus use; and a planned activity that would prevent bus use for greater than two weeks during the four month intervention phase of the 10 month study period e.g. surgery, extended holiday.

**Fig. 2 fig2:**
[figure not shown]
Overview of participant timeline.

## Interventions

7

The *trips4health* study has a four-month intervention phase followed by a six month maintenance phase (Fig. 2). While there is debate in the literature about the minimum length of time needed for habits to form [29] a four-month intervention phase was selected as it allows three months for behaviour change to reach automaticity and one month for maintenance or ‘tapering off’, where contact and support is gradually withdrawn in preparation for intervention cessation [30] (Table 1). Using a ‘gain-framed’ approach (i.e. rewarding positive behaviours), participants in the intervention group will have bus trip targets from weeks 1–16 which escalate over the course of the intervention so that targets become more difficult to reach but incentive values increase. If the bus trip target is met (confirmed through objective smartcard data), participants receive bus trip credit (through their smartcard). The credit received will be commensurate with the participant's default/usual fare type that they were required to set when applying for their smartcard. The price range (AUD$) of the different fare types is $1.92 to $5.76 (a concessional fare through to a full-fare with travel across multiple zones). The maximum credit a participant can receive by the end of the 16-week intervention phase is $103.68 if travelling on a concessional fare and if travelling on a full-fare either $151.20, $207.36 or $311.04 as per their default fare type. Participants will be notified by a weekly email whether they have met or have not met their target, the smartcard credit they have received (if any) and the following week's target. Participants will be aiming to achieve five one-way bus trips per week by the end of the intervention. To assist participants to achieve the weekly targets and, consistent with best practice, incentives will be supported by other behaviour change techniques (e.g. information on consequences of behaviour to the individual, setting graded tasks, goal setting, social support), delivered via weekly mobile text messages [31]. Development of the text messages was underpinned by the Behaviour Change Technique Taxonomy, informed by our previous qualitative work on transport behaviour and PA and from an incentive-based study designed to increase weekly leisure-time PA and reduce sitting time [14,22,32]. Text messages will be offered to the intervention group only. This can help to counter the potential risk that incentives alone may undermine intrinsic motivation in the absence of broader behavioural support. It has been argued that incentives aimed at addressing habitual behaviours such as physical inactivity may be more impactful if delivered as part of effective behaviour change programs [31]. Both the intervention and control groups will receive printed versions of Australia's Physical Activity and Sedentary Behaviour Guidelines [33]. Educational materials have been selected as an active control to help engage and retain the control group – alone, this type of cognitive strategy is unlikely to influence PA behaviour [34]. All intervention support will be provided by a member of the research team.

**Table 1 tbl1:** *trips4health* intervention schedule.

	Intervention phase	Bus trip targets	Smartcard credit available (all zones full-fare^a^)	Smartcard credit available (all zones concessional fare^b^)	Text message frequency
Within 2 weeks pre-intervention	*Baseline survey, smartcard data, clinic assessment, accelerometer, travel behaviour smartphone app*				
Week 1	Getting started	1	$5.76	$1.92	x 2
Week 2	Getting started	1	$5.76	$1.92	x 2
Week 3	Slowly increasing	2	$11.52	$3.84	x 2
Week 4	Slowly increasing	2	$11.52	$3.84	x 2
Week 5	Moving along	3	$17.28	$5.76	x 2
Week 6	Moving along	3	$17.28	$5.76	x 2
Week 7	Moving along	3	$17.28	$5.76	x 2
Week 8	Moving along	3	$17.28	$5.76	x 2
Week 9	Aiming high	4	$23.04	$7.68	x 2
Week 10	Aiming high	4	$23.04	$7.68	x 2
Week 11	Aiming high	4	$23.04	$7.68	x 2
Week 12	Aiming high	4	$23.04	$7.68	x 2
Week 13	Keeping up	5	$28.80	$9.60	x 1
Week 14	Keeping up	5	$28.80	$9.60	x 1
Week 15	Keeping up	5	$28.80	$9.60	x 1
Week 16	Keeping up	5	$28.80	$9.60	x 1
***Total***		**54**	**$311.04** (AUD)	**$103.68** (AUD)	**28**
Week 17 or 18	*Post-intervention survey, smartcard data, clinic assessment, accelerometer, travel behaviour smartphone app*				
Week 41 or 42 >(10 months from baseline)	*Follow-up survey, smartcard data, clinic assessment, accelerometer, travel behaviour smartphone app*				

a most expensive fare type.

b cheapest fare type. 50% of the public transport provider's adult passengers travel on a concessional fare.

## Outcomes

8

The primary outcome is change in average daily step count measured by accelerometer over seven days at baseline (Timepoint 1/T1), immediately post-intervention (week 17/18; Timepoint 2/T2; primary endpoint) and at the end of the maintenance phase (week 41/42; Timepoint 3/T3). The secondary outcomes are change in: self-reported and measured (via a smartphone app collected over seven days and smartcard data) travel behaviour (e.g. mode (e.g. motor vehicle), frequency and duration); perspectives on travel behaviour (e.g. enablers and barriers); self-reported out of pocket transport-related expenses; self-reported work productivity; self-reported commute time to work/study location; self-reported commute time by different transport modes; self-reported PA (transport, leisure, occupational, domestic, total) (mins/week) and sedentary behaviour (sitting) using the International Physical Activity Questionnaire – Long form (IPAQ – L) supplemented with additional questions in the study-specific survey [35]; accelerometer measured minutes/week of PA, sedentary behaviour and PA intensity; measured blood pressure using a validated automated blood pressure device and waist circumference determined by a measurement tape; body mass index calculated from measured (using a stadiometer and digital scales) or self-reported height and weight; and self-reported health, with quality of life (QoL) measured by the Assessment of Quality of Life (AQoL)-8D [36,37]. Costs incurred by the public transport provider to implement the intervention will be measured by data supplied by the provider at trial completion. All self-reported outcomes will be measured through the study-specific survey at all three timepoints.

## Sample size

9

Sample size calculations are based on the comparison of the primary outcome in the control versus intervention group. The calculations are based on mean and standard deviation of daily steps as measured by accelerometer (8000 ± 3500) based on data from a sample of participants using the same measure [38]. The assumed correlation between baseline and at 10 months follow-up was 0.7, with a high level of stability expected between baseline and follow-up because PA typically tracks well over shorter periods of time (e.g. weeks and months) [39]. A high level of stability is expected between baseline and at 10 months follow-up because the unit of analysis will be based on average daily steps. A total sample of 300 participants would provide 80% power with α = 0.05 to detect a difference of 624 steps/day (an 8% change). Allowing for expected attrition (based on a previous related PA incentives-based study [14]), the plan is to recruit 350 participants.

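### Section 9 ties its correlation to 10 months although the primary endpoint is at four months, and its 80% power for 624 steps/day does not follow from its own inputs at either time point

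*Protocol article*

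**What the plan says.** Section 8 (Outcomes) lists three measurement times and labels one of the follow-ups as primary: "immediately post-intervention (week 17/18; Timepoint 2/T2; primary endpoint". The 10-month assessment is placed "at the end of the maintenance phase (week 41/42; Timepoint 3/T3".

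Section 9 (Sample size) opens with "Sample size calculations are based on the comparison of the primary outcome in the control versus intervention group", so the calculation is presented as a between-group one for the primary outcome. Its inputs are "daily steps as measured by accelerometer (8000 ± 3500") and "The assumed correlation between baseline and at 10 months follow-up was 0.7". The next sentence ties the expected stability to 10 months again. The supporting argument is that "PA typically tracks well over shorter periods of time (e.g. weeks and months"). The result is "A total sample of 300 participants would provide 80% power" at alpha 0.05 for a difference of 624 steps/day, described as 8% (624/8000 = 7.8%). Recruitment is set at 350 to allow for attrition.

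The Methods paragraph of the abstract says "The primary outcome is change in accelerometer measured average daily step count at baseline and four- and ten-months later" and does not say which follow-up is primary.

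**The concern.** The correlation is the only input in section 9 that is tied to a time point, and that time point is not the primary one. A reader who wants the power of the T2 comparison has no T2 correlation to work with.

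The second problem appears when the calculation is repeated. The stated N, SD and correlation do not give 80% power for 624 steps/day in a two-group comparison, whichever follow-up is meant. If the trial ends with a non-significant T2 result, readers will take it as evidence from a study with an 80% chance of detecting 624 steps/day. On the stated inputs that chance was closer to one half.

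**Working it through.** **Inputs.** From section 9: SD 3500, correlation r = 0.7, total 300, alpha 0.05, power 80%, difference 624. From section 11.1: 1:1 allocation, so 150 per arm. Sidedness is not stated and two-sided is assumed. The formula is not stated either, so the usual candidates are tried.

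**Effective SD.**
- Change score: 3500 × √(2 × (1 − 0.7)) = 2711
- Baseline-adjusted (ANCOVA): 3500 × √(1 − 0.7²) = 2500
- Follow-up value only: 3500

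Section 12.3 plans a linear mixed model. For one follow-up contrast in complete data, the change-score and baseline-adjusted versions are the natural approximations to it.

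**Attempt to reproduce 624 at 80% power.** Detectable difference = (1.960 + 0.842) × SD × √(2/150).

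| Analysis | Detectable difference | Power for 624 | Total N for 624 |
|---|---|---|---|
| Change score | 877 (exact t: 880) | 51% | 594 |
| Baseline-adjusted | 809 (exact t: 811) | 58% | 504 |
| Follow-up only | 1132 | 34% | 988 |

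None gives 624. A one-sided test raises power only to 64% (change) or 70% (baseline-adjusted). Averaging both follow-ups with baseline adjustment, taking all pairwise correlations as 0.7, gives 73% two-sided and 82% one-sided (N = 282). Neither matches 300, and an average is not the T2 endpoint. A one-sided change to the mean of both follow-ups does detect 624, but with 350 people analysed, not 300.

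**What does match at the stated N.** A one-sample paired t-test on 150 people with a change SD of 2711 has 80% power at 624.2 steps/day. That is a change within one arm of 150. The variance of a difference between two such arms is twice as large, so the detectable difference is √2 times larger: 624 × 1.414 = 882, in line with the 880 above. That 624 arose this way is an inference from the match; the document does not say so.

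**Effect of the time point.** Time enters only through r. The documents give no baseline-to-four-month correlation, so a range is assumed (150 per arm, two-sided, power for 624, normal approximation):

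| r (baseline to T2) | Change score | Baseline-adjusted |
|---|---|---|
| 0.6 | 40.8% | 48.8% |
| 0.7 | 51.3% | 58.0% |
| 0.8 | 68.5% | 73.0% |
| 0.85 | 80.5% | 83.4% |
| 0.9 | 93.2% | 94.3% |

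**Correlation needed.** Reaching 624 with 80% power needs an effective SD of 624 / (2.802 × √(2/150)) = 1929. That means r = 1 − (1929/3500)²/2 = 0.85 for change scores, or r = √(1 − (1929/3500)²) = 0.83 with baseline adjustment.

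**The case against.** The strongest reply is that the time label does no harm. Correlations usually weaken as the interval lengthens, and section 9's own remark about tracking over shorter periods points the same way. A 10-month value would then, if anything, be conservative for four months. If the two correlations are equal, nothing changes. This stands. A reader might infer that using the 10-month correlation is what overstates the power, but the documents do not support that: the shortfall at r = 0.7 is identical at T2 and T3. It would also be wrong to say that no plausible correlation reaches 624, since values of about 0.83 to 0.85 and above do. The protocol does not claim such a value.

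Two further readings are tempting. One is that T2 and T3 both remain candidates for the deciding test, so that the false-positive rate exceeds 5%. Section 8 labels T2 alone as the primary endpoint, section 12.1 describes T3 as showing whether changes last once incentives stop, and no rule lets either time point claim success. The abstract's silence is a matter of clarity. The other is that the September and February recruitment waves make the four-month correlation lower through seasonal change. The documents give no seasonal figures, a shift shared by a whole wave does not by itself lower the correlation within that wave, and section 10 gives lessening the impact of seasonal variation as one reason for having two waves.

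It could also be said that calculation details belong in a fuller document. That would excuse a missing formula. It does not excuse printed inputs and a printed result that disagree.

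**Conclusion.** The point holds in two parts. First, section 8 places the primary endpoint at four months, while section 9 ties the correlation in its primary-outcome calculation to 10 months. This is a real inconsistency, with no demonstrated effect on power by itself. Second, and more important, the stated power is not what the design delivers on its stated inputs. At 300 analysed, 80% power corresponds to about 811 steps/day (10.1% of 8000) baseline-adjusted or 880 (11.0%) on change scores, and power for 624 is about 58% or 51%.

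These figures rest on a two-sided test, equal SDs of 3500 in both arms and at both times, 150 analysed per arm, and a T2 correlation of 0.7. The last is the protocol's 10-month value carried over for want of a four-month one. A documented T2 correlation of about 0.83 to 0.85 would restore the claim. Changing only the time label would leave the main error in place.

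**What to change.** Restate the section 9 calculation for the between-group contrast at T2. Give the baseline-to-four-month correlation with its source, the formula and the sidedness. Report what follows at 300 analysed: on present inputs, either a detectable difference of about 811 to 880 steps/day at 80% power, or power of about 51% to 58% for 624. Give the T3 calculation separately, with the 10-month correlation, as secondary. In the abstract, name four months as the primary time point.

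This is a change to the text of section 9 and the abstract. It needs no extra enrolment, because it corrects what is claimed for the planned sample. The downside is a less favourable stated figure. Keeping both 624 steps/day and 80% power at r = 0.7 would instead need about 504 (baseline-adjusted) or 594 (change score) analysed; that is a separate design decision for the sponsor.

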### Allocation

11.1

After completion of the baseline assessment (T1), participants will be randomly allocated to the control or intervention arm. The allocation sequence will be created using computer-generated random numbers on a 1:1 ratio without stratification. Randomisation will be conducted in blocks of four, the details of which will be unavailable to research team members who enrol participants in the respective study arms.

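### The stated 80% power for 624 steps/day does not follow from the protocol's own inputs: power for the between-arm comparison is about 51% to 58%

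*Protocol article*

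**What the plan says.** The Sample size section opens by fixing the comparison: "Sample size calculations are based on the comparison of the primary outcome in the control versus intervention group". It takes a "mean and standard deviation of daily steps as measured by accelerometer (8000 ± 3500" and adds: "The assumed correlation between baseline and at 10 months follow-up was 0.7". The result is then given: "A total sample of 300 participants would provide 80% power with α = 0.05" "to detect a difference of 624 steps/day (an 8% change". Allowing for attrition, "the plan is to recruit 350 participants".

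Three other places bear on the calculation. Under Allocation: "The allocation sequence will be created using computer-generated random numbers on a 1:1 ratio without stratification". That makes 150 per arm. Under Outcomes, the primary endpoint is the T2 assessment, "immediately post-intervention (week 17/18; Timepoint 2/T2; primary endpoint". Under Statistical methods, the primary analysis is a linear mixed model comparing the two groups. The article does not say whether the test is one- or two-sided, and it shows no sample-size formula.

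**The concern.** All the inputs needed for a two-arm calculation are printed, and so is the result, so the result can be checked. A detectable difference of 624 looks too small for 150 per arm with an SD of 3500 and a correlation of 0.7. This is not a matter of detail left to a fuller document, because the article states both the inputs and an answer that should follow from them.

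This sentence is the article's only justification for analysing 300 and recruiting 350. If it is wrong, a true effect of 624 steps/day would be missed in roughly 42% to 49% of repetitions of the trial, against the 20% that 80% power implies.

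**Working it through.** **Inputs.** SD 3500, r = 0.7, total 300, α = 0.05, power 80% (Sample size); 1:1 allocation, so n = 150 per arm (Allocation). Assumption: two-sided test, so the multiplier is 1.960 + 0.842 = 2.802. The correlation of 0.7 is applied to T2, although the article gives it for baseline to 10 months.

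**Step 1: trying to reproduce 624 as a between-arm difference.**

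- Change score: SD = 3500 × √(2 × (1 − 0.7)) = 2711. Standard error of the difference = 2711 × √(2/150) = 313.0. Detectable difference = 2.802 × 313.0 = 877 (880 with the t distribution).
- Baseline-adjusted: SD = 3500 × √(1 − 0.7²) = 2500. Standard error = 2500 × √(2/150) = 288.6. Detectable difference = 2.802 × 288.6 = 809 (811 with t).

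A linear mixed model can behave like either of these, depending on how baseline is handled, so both are shown.

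**Step 2: power at 624.**

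- Change score: 624/313.0 = 1.993; 1.993 − 1.960 = 0.033; power 51.3% (51.1% with t).
- Baseline-adjusted: 624/288.6 = 2.162; 2.162 − 1.960 = 0.202; power 58.0% (57.7% with t).

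**Step 3: variants that might rescue the claim at a single follow-up.**

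| Variant | Change score | Baseline-adjusted |
|---|---|---|
| Two-sided, 150 per arm: power at 624 | 51% | 58% |
| One-sided, 150 per arm: power at 624 | 64% | 70% |
| Two-sided, 175 per arm (all 350): power at 624 | 57% | 64% |
| One-sided, 175 per arm: detectable difference | 721 | 664 |
| Two-sided, 150 per arm: power at 640 (exactly 8% of 8000) | 53% | 60% |
| Correlation needed for 80% power at 624, two-sided, 150 per arm | 0.85 | 0.83 |
| Per-arm n needed for 80% power at 624, two-sided (t) | 298 | 253 |

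Follow-up values alone, ignoring baseline, give 34%.

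**Step 4: where 624 could come from.** A paired test of change within one group of 150 has standard error 2711/√150 = 221.4. With the t distribution the detectable change is 624.2, and power at 624 is 79.98%. Two other slips come close under the normal approximation. Using 3500 × √(1 − 0.7) = 1917 as the SD of a two-arm comparison gives 1917 × √(2/150) × 2.802 = 620. Reading 300 as the number per arm, with change scores, also gives 620. In all three, the variance of the between-arm difference is half what it should be.

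**The case against.** **The mixed model uses two follow-ups.** Averaging T2 and T3 reduces the variance. With all correlations at 0.7 and a two-sided test, power at 624 rises to 63% (change) or 73% (baseline-adjusted). It gets to about 80% only if the T2–T3 correlation is 0.6 or lower (79% at 0.6, 86% at 0.5). The article states no such value, and it would lie below the 0.7 assumed over the longer span from baseline to 10 months. Combining the average with a one-sided test does reach 80%: baseline-adjusted power is 82% at 150 per arm, and change scores give 624 with 175 per arm. But the first does not reproduce 624 (its detectable difference is 603), the second uses 350 where the article says 300, and neither is the T2 endpoint. This defence fails for the claim as printed.

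**The correlation at T2 may be higher than 0.7.** This has some force. The article itself argues that activity tracks well over shorter periods, and T2 is nearer to baseline than 10 months. At r = 0.8 the baseline-adjusted SD is 3500 × √(1 − 0.64) = 2100 and the detectable difference about 680. So 51% to 58% is conditional on r = 0.7 and not a fixed property of the trial. Even 0.8 falls short of what 624 requires.

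**Stronger readings.** A reader might infer that the calculation was certainly done for one arm only. The match is close, but no formula is shown, the text says control versus intervention, and other slips land within 1%. A reader might also infer that about 810 steps/day is out of reach for this intervention; the article gives no steps-per-trip figure from which to judge that. Nor does it contain any rule by which a null result would be taken to exclude an 8% effect. Interpretation would rest on the estimate and its confidence interval, which a planning error does not bias.

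**Conclusion.** The power statement is wrong as written. On the stated SD, correlation, total and allocation, 300 participants have about 51% to 58% power for a between-arm difference of 624 steps/day, and 80% power for about 880 (change score) or 811 (baseline-adjusted). The detectable difference is understated by 187 to 256 steps/day (811 − 624 and 880 − 624).

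The power figures rest on two assumptions: a two-sided test, and r = 0.7 carried over to T2. Relaxing the first does not restore 80%; relaxing the second does so only at about 0.83 to 0.85, a value the article does not give. The loss of a factor of two in the variance is the likely explanation, and the conclusion does not depend on it. The finding concerns the design claim; it does not make the planned analysis invalid.

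**What to change.** Keep the recruitment target of 350 and replace the power sentence, for example with:

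> With 300 participants analysed (150 per arm), the trial has 80% power at two-sided α = 0.05 for a between-group difference of about 810 steps/day (10%) in a baseline-adjusted analysis, taking SD 3500 and r = 0.7 (the value assumed for baseline to 10 months, applied here to the T2 primary endpoint). Power for 624 steps/day is about 58%.

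If the mixed model will in effect compare change scores, the matching figures are 880 steps/day (11%) and 51%.

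The cost is wording and a less favourable headline figure; no participants are added and the analysis does not change. If the sponsor instead wants to keep 80% power at 624, it needs either a justified T2 correlation of about 0.83 to 0.85, or 506 (2 × 253) to 596 (2 × 298) analysed participants. At the attrition implied by 300 out of 350, that means recruiting about 590 (506 × 350/300) to 695 (596 × 350/300).
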